#### Questionnaires

For all participants in the Tango-DM trial, questionnaires will be administered at 3 time points: study inclusion, around 36 weeks of pregnancy and 4–6 weeks postpartum.

Quality of life will be measured using the EuroQol (EQ-5D-5 L) at a gestational age of 36 weeks and 6 weeks post-partum. The EQ-5D-5 L assesses 5 domains (mobility, self-care, usual activities, pain/discomfort, anxiety/depression) with 5 possible answer levels ranging from “no problems” to “severe problems” [26].

Mood will be scored using the Edinburgh Postnatal Depression Scale (EPDS) at inclusion and post-partum. The EPDS has 7 questions regarding depression and anxiety [27].

The questionnaires will take approximately 10–30 min to complete.

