#### Randomization

Randomization to the intervention arm or comparator arm will be done on a 1:1 basis, using the online software tool Castor EDC (www.castoredc.com, Castor EDC, Ciwit B.V., the Netherlands and Castor Research Inc, USA). Castor EDC complies with all applicable laws and regulations. Block stratified randomization will be used, with stratification for center and alternating variable block lengths of 2 and 4 with a block size unknown to the site. The trial is not blinded: health care providers and participants will be aware of their OGTT results and their allocation group.

We will register age, parity, prepregnancy BMI, prior GDM and ethnicity for women not consenting to randomization in the TANGO-DM trial.

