Missing cost and effect data will be imputed using multiple imputation according to the MICE algorithm developed by van Buuren [33]. Rubin’s rules will be used to pool the results from the different multiply imputed datasets. Bivariate regression analyses will be used to estimate cost and effect differences between intensive GDM treatment and normal obstetric care while adjusting for confounders if necessary. Incremental cost-effectiveness ratios (ICERs) will be calculated by dividing the difference in the mean total costs between the treatment groups by the difference in mean effect between the treatment groups. Bias-corrected and accelerated bootstrapping with 5000 replications will be used to estimate 95% confidence intervals around the cost differences and statistical uncertainty surrounding the ICERs. Uncertainty surrounding ICERs will be graphically presented on cost-effectiveness planes. Cost-effectiveness acceptability curves will also be estimated showing the probability that, in pregnant women with discordant OGTT results, intensive GDM treatment is cost-effective in comparison to normal obstetric care for a range of different ceiling ratios thereby showing decision uncertainty [34].

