#### Planned analyses

Baseline characteristics will be presented as frequencies and percentages in each group, or as averages (mean or median) with standard deviations or interquartile ranges as appropriate. The primary outcome will be evaluated by estimating the relative risk between both treatment arms. Analyses will be conducted in both the intention-to-treat and per protocol population for the primary outcome.

Relative risks will be estimated for categorical outcomes, with 95% confidence intervals, and χ2 tests for significance. Fisher’s exact test will be used for sparse events where assumptions of the χ2 test are not met. Continuous data will be described as means with standard deviation if normally distributed, or medians with interquartile ranges when not normally distributed; tests for significance are t-tests or Mann-Whitney U tests, respectively. The Hodges-Lehman estimator will be used to calculate the confidence interval for the difference in medians.

Individuals who were randomized to normal obstetric care but for unknown reasons received treatment they will be excluded from the per protocol analysis. If the treatment followed an abnormal repeat OGTT they will remain in the per protocol analysis. Individuals who were randomized to GDM treatment but for unknown reasons never received treatment will be excluded from the per protocol analysis. If, per example, they did not receive treatment because of preterm birth they will remain in the per protocol analysis.

Subgroup analyses will be performed for BMI (under or above 30 kg/m2), early or late GDM (before or after 24 weeks) and according to the result of the OGTT (abnormal fasting result, abnormal postprandial result, or both).

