## Discussion

The TANGO-DM trial is the first to provide randomized evidence on the effectiveness and cost-effectiveness of intensive GDM treatment versus no treatment in a group of women that would formerly i.e. before the new (2013) WHO criteria would not have been diagnosed as GDM, and subsequently would not have received treatment. It will provide guidance for the justification of these new diagnostic criteria and the study results will have important clinical implications. Moreover, the cohort formed by participants of the TANGO-DM trial provides an opportunity to assess differences in long-term health outcomes mothers and their offspring after treatment of no treatment.

Strengths of this trial include the large sample size and randomized design. We will report on all core outcome measures defined for GDM studies and, next to the effectiveness manuscript, provide a cost-effectiveness analysis [29]. The study did not proceed as originally planned due to the impact of the complexities associated with managing a large, multidisciplinary trial. The study involved multiple disciplines, including gynecology, midwifery, internal medicine, and clinical chemistry, which added complexity to its execution.

A limitation of this study may be non-compliance with voluntary questionnaires sent during pregnancy and the postpartum period. Compliance to fill in the questionnaires will be enhanced by sending questionnaires per email that can be filled in online and are compatible with smartphone.

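### Minor free gain in precision: the general rule for continuous data, if applied to the postpartum EPDS, is valid but leaves the inclusion EPDS unused

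*Protocol article*

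**What the plan says.** The Questionnaires section of the protocol article sets the schedule: "questionnaires will be administered at 3 time points: study inclusion, around 36 weeks of pregnancy and 4–6 weeks postpartum". For the EPDS it adds: "Mood will be scored using the Edinburgh Postnatal Depression Scale (EPDS) at inclusion and post-partum". It is the only questionnaire score stated for both inclusion and postpartum; the EQ-5D-5L is stated for 36 weeks and 6 weeks postpartum.

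The section Planned analyses has one rule for continuous data: "tests for significance are t-tests or Mann-Whitney U tests, respectively", chosen by whether the data look normal. For medians, "The Hodges-Lehman estimator will be used to calculate the confidence interval for the difference in medians". None of these uses a baseline value.

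Covariate adjustment appears only under Cost-effectiveness: "Bivariate regression analyses will be used to estimate cost and effect differences" between the arms, "while adjusting for confounders if necessary". The effect measures listed there are LGA, the perinatal and maternal outcomes, and QALYs.

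The EPDS is not in Table 2, not in the list of baseline characteristics, and not among the instruments under Burden of treatment. No section gives it an analysis of its own.

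**The concern.** A score measured before and after allocation can be compared between arms more precisely if the earlier value enters the model. On the text shown, the inclusion EPDS is collected but given no use.

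What is at stake is precision on one secondary questionnaire score. It has some value here because the Discussion expects "non-compliance with voluntary questionnaires sent during pregnancy and the postpartum period", so the number of postpartum responders may fall well short of the number randomized. Neither the validity of the unadjusted test nor the primary result is in question.

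**Working it through.** **The plan's own figure.** No power or sample size is stated for the EPDS. The only one is for LGA, 16% versus 10%, 80% power, alpha 5% (taken as two-sided), 5% loss. With unpooled variance:

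(1.960 + 0.842)² × (0.16×0.84 + 0.10×0.90) / 0.06² = 489.3, so 490 per arm; 490/0.95 = 515.8, so 516 per arm and 1032 in total.

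This matches the article. The EPDS point does not touch it.

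**Validity of the unadjusted test.** The article states "Randomization to the intervention arm or comparator arm will be done on a 1:1 basis", with individual randomization. A two-sample comparison of postpartum scores is therefore unbiased with correct type I error, given complete follow-up. Non-response to the postpartum form is a separate matter that affects adjusted and unadjusted analyses alike.

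**Precision.** Let ρ be the correlation between inclusion and postpartum EPDS, and m the share of postpartum responders without a usable inclusion score, missing at random. Both are assumed, since the documents give neither. Standard error (SE) relative to the unadjusted comparison:

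- Linear model, unusable inclusion scores set to the overall mean: √(1 − (1 − m)ρ²).
- Linear model, complete cases only: √((1 − ρ²)/(1 − m)).

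Reduction in SE with overall-mean fill:

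| m | ρ = 0.3 | ρ = 0.5 | ρ = 0.7 |
|---|---|---|---|
| 0 | 4.6% | 13.4% | 28.6% |
| 0.10 | 4.1% | 12.0% | 25.2% |
| 0.25 | 3.4% | 9.9% | 20.5% |
| 0.50 | 2.3% | 6.5% | 13.1% |

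For example, at ρ = 0.5 and m = 0.25: √(1 − 0.75×0.25) = √0.8125 = 0.901.

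Dropping women without an inclusion score would undo the gain. At m = 0.25 the complete-case factor is 1.102, 1.000 or 0.825 at ρ = 0.3, 0.5 or 0.7, so the SE is 10.2% larger, equal, or 17.5% smaller.

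**Detectable difference at 80% power**, 2.802 × √(2/n) × factor, at ρ = 0.5 and m = 0.25:

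- n = 490 per arm (the evaluable number for LGA, optimistic for a voluntary questionnaire): 0.179 SD unadjusted, 0.179 × 0.901 = 0.161 SD adjusted.
- n = 258 per arm (assumed, half of 516): 0.247 SD and 0.222 SD.

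**Simulation check** (258 per arm, 4000 runs, true difference 0.20 SD, ρ = 0.5, m = 0.25). The mean-fill model gave a mean estimate of 0.200 and 94.8% interval coverage. Empirical SEs were 0.0886 unadjusted, 0.0794 mean fill and 0.0881 complete case. A repeat gave 0.088, 0.080 and 0.089, with 95.0% coverage.

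**Skewed score.** With a rounded gamma score cut at 0 to 21 (an assumed shape), 258 per arm, 2000 runs and m = 0.25, power was:

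| latent ρ | t-test | Mann-Whitney | linear model |
|---|---|---|---|
| 0.3 | 0.65 | 0.66 | 0.67 |
| 0.5 | 0.66 | 0.68 | 0.74 |
| 0.7 | 0.67 | 0.68 | 0.82 |

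**Late inclusion forms.** The trial is open label, so a form filled in after allocation could reflect the diagnosis. With 25% late and an assumed shift of 0.2 SD in treated women, the mean estimate of a true 0.20 was 0.202 if late scores were set to missing and 0.177 if they were kept.

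**The case against.** The strongest objection is that the article fixes no EPDS analysis, so there is no poor choice to criticise. The score is in neither Table 2 nor the economic effect measures, and the article does not even say whether it will be analysed as continuous or categorical. Applying the general rule to it is an inference. Baseline adjustment of a secondary score is also ordinary content for a statistical analysis plan or the full protocol, neither of which is shown. Most of this stands, and it is why the point is conditional and framed as an improvement. What survives is that the article's one stated rule for continuous data, followed as written, uses no baseline.

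The size is open to the same criticism: every correlation and missingness rate is assumed, and at ρ = 0.3 the power gain over Mann-Whitney is 0.66 to 0.67, which is negligible. That also stands.

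A reader might infer that the planned regressions in the economic evaluation show an inconsistency, with adjustment accepted in one place and refused in another. The documents do not support this. Those models concern costs and listed effects, adjust for confounders if needed, and do not cover the EPDS.

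Finally, the article does not say whether the inclusion form precedes allocation. This limits how many inclusion scores are usable, but not whether the method is valid. Completion before randomization cannot depend on arm, so restricting to those scores and filling the rest with the overall mean stays valid however many forms are late.

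**Conclusion.** The point holds as a minor, nearly free improvement. If the general rule is applied to the postpartum EPDS, the comparison is valid but less precise than the collected data allow. Under assumed ρ of 0.3 to 0.7 and 0 to 50% unusable inclusion scores, the loss is about 2% to 29% of the SE. The gain is small at 0.3 and moderate at 0.5.

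A reader might go further and infer that the EPDS comparison is biased, or that the authors have committed to an unadjusted analysis. Neither follows: randomization protects the unadjusted test, and the article commits to no EPDS analysis. The LGA analysis and the 1032 sample size are unaffected.

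**What to change.** Prespecify, before EPDS data are examined by arm:

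- A linear model for postpartum EPDS with arm and inclusion EPDS, in all postpartum responders by allocated arm, reporting the adjusted mean difference with 95% CI.
- Only inclusion scores completed before randomization are used, checked from form dates. Later or absent scores are set to the overall mean, not the mean by arm, so that no postpartum responder is dropped.
- The unadjusted t-test or Mann-Whitney comparison may be reported as a sensitivity analysis. The main analysis for this score should not switch according to how many forms turn out to be late.

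The cost is about two lines in the analysis section, a little more analysis work and one check of form dates against randomization dates. No new data or visits are needed, and nothing changes for enrolled women. If the analysis plan already specifies this, no action is needed.

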#### Randomization

Randomization to the intervention arm or comparator arm will be done on a 1:1 basis, using the online software tool Castor EDC (www.castoredc.com, Castor EDC, Ciwit B.V., the Netherlands and Castor Research Inc, USA). Castor EDC complies with all applicable laws and regulations. Block stratified randomization will be used, with stratification for center and alternating variable block lengths of 2 and 4 with a block size unknown to the site. The trial is not blinded: health care providers and participants will be aware of their OGTT results and their allocation group.

We will register age, parity, prepregnancy BMI, prior GDM and ethnicity for women not consenting to randomization in the TANGO-DM trial.

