**Methods:**

The TANGO-DM trial is an open label, multicenter randomized controlled trial. Participants are pregnant with a gestational age between 16 + 0 and 32 + 0 weeks, who underwent a 1-step venous 2- or 3-point 75-gram oral OGTT, were eligible if they had glucose concentrations discordant between the old (1999) and the new (2013) criteria. After informed consent, women are randomized to either intensive GDM treatment, consisting of dietary advice and glucose monitoring and, if euglycemia is not reached, antihyperglycemic agents, or normal obstetric care without GDM treatment. The primary outcome is large-for-gestational-age infants (birth weight > 90th percentile). Secondary outcome measures include maternal complications, obstetric complications, neonatal complications, obstetric interventions, quality of life, and healthcare and societal costs. Outcomes will be analyzed according to the intention-to-treat principle. The study is powered to detect a reduction in LGA from 16% in the untreated to 10% in the treated group, which requires 1032 participants (516 per arm; alpha-error 5% for 80% power).

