**Fig. 2 Fig2:**
[figure not shown]
Flowchart screening and study procedures

Eligible patients will be informed and invited to participate by either their diabetes care or obstetric care provider, i.e. physician, obstetrician, midwife, or diabetes nurse. Following counselling, written informed consent is obtained. Sufficient recruitment depends on the applicability of our assumptions of the number of pregnant women with discordant OGTT results. Based on work from the Netherlands, a conservative estimate of the percentage of women with a discordant blood glucose concentration after OGTT is around 9–15% [21].

Participants of the study will be randomized between:Intensive GDM treatmentNormal obstetric care

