### Ethics and dissemination

The Medical Research Ethics Committee (MREC) of the Amsterdam UMC, location AMC approved this trial. Trial reference number: METC 2018_173. Changes to the study protocol are documented in amendments. Amendments are submitted for approval to the MREC. Major changes will be updated on the trial registration website [37]. The full study protocol, including amendments, is publically available on the study website [38].

After completion of the trial the core investigators will report on the results of the main study and submit a manuscript to a peer-reviewed medical journal. Supplementary analyses will be reported separately.

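### Centre-stratified blocks of only 2 and 4 in an open-label trial make allocation partly predictable, and the sentence that relies on an unknown block size also prints it

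*Protocol article*

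**What the plan says.** The Randomization section of the protocol article fixes the scheme. "Randomization to the intervention arm or comparator arm will be done on a 1:1 basis", "using the online software tool Castor EDC". "Block stratified randomization will be used, with stratification for center", and the blocks have "alternating variable block lengths of 2 and 4 with a block size unknown to the site". The section then adds: "The trial is not blinded: health care providers and participants will be aware of their OGTT results and their allocation group".

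Three other places bear on the point:

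- Recruitment and study procedure: "Eligible patients will be informed and invited to participate by either their diabetes care or obstetric care provider". The people who recruit are therefore people who treat.
- Abstract, Methods: "After informed consent, women are randomized", so consent comes before allocation.
- Ethics and dissemination: "The full study protocol, including amendments, is publically available on the study website". The article does not say whether that document also gives the block lengths.

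The article does not use the word concealment. The only protection it names against prediction is that sites do not know the block size.

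**The concern.** In an open-label trial, every past allocation at a centre can be known to its staff. With a separate list per centre and blocks of 2 and 4, the running count of the two arms returns to equality every two or four women, so the arm that is behind is a strong clue to the next allocation. The recruiter also has the OGTT values in hand when inviting.

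A recruiter who expects a given arm could approach, delay or not approach a woman according to her apparent risk of a large-for-gestational-age (LGA) infant. The arms would then differ at baseline in a way that intention-to-treat analysis does not correct, because the selection happens before randomisation. The Planned analyses section gives a relative risk and a χ² test for the primary outcome and names no check of this kind.

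**Working it through.** **Inputs.** From the Randomization section: ratio 1:1, strata by centre, lengths 2 and 4, no blinding. From the Sample size section: LGA 16% versus 10%. The number and size of centres are not given, so 10 to 100 women per centre is an assumed range. The document gives no figure for predictability to reproduce. Its sample size does reproduce: with unpooled variance, (1.960 + 0.842)² × (0.16×0.84 + 0.10×0.90)/0.06² = 489.2, so 490 per arm, and 490/0.95 = 516. Nothing below changes it.

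**1. Guessing from a tally alone.** Every block ends balanced, so the centre's running imbalance equals the imbalance within the current block. The rule is to name the arm that is behind and toss a coin when the arms are level.

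- Block of 2: 0.5 + 1 = 1.5 correct.
- Block of 4: first 0.5; second 2/3; third (1/3)×1 + (2/3)×0.5 = 2/3; fourth 1. The sum is 2.833.
- Together: (1.5 + 2.833)/6 = 72.2%.

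This needs no knowledge of lengths or of their order. The arms are unequal at 1 + (1 + 1/3 + 1) = 3.333 of 6 positions (56%), and there the guess is right 3/3.333 = 90% of the time.

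**2. Allocations certain in advance, lengths known.** The wording can mean strict alternation or random variation, so both readings are shown.

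- *Random order.* The imbalance reaches 2 only at the midpoint of a block of 4, with probability 2/6 = 1/3, and the next two allocations are then forced. Per pair of blocks: (2 × 1/3)/6 = 11.1%. Simulation gives 10% to 11% for 10 to 100 women per centre.
- *Strict alternation, position known.* The certain allocations are 1 per block of 2 and 4/3 per block of 4: (1 + 1.333)/6 = 38.9%.
- *Strict alternation, starting length inferred from the sequence* (simulation, 5,000 sequences per centre size): 21% at 10 women, 28% at 20, 32% at 40, 36% at 100.

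**3. Comparison with randomly ordered blocks of 4, 6 and 8.**

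| | 2 and 4 | 4, 6 and 8, random order |
|---|---|---|
| Correct guesses | 72% | 68% |
| Correct when arms are unequal | 90% | 78% |
| Certain in advance | 11% (random) to 39% (alternating, position known) | about 2% |

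The 68% is (2.833 + 4.1 + 5.329)/18. Uncertainty about block ends barely lowers it, because the tally rule does not use block ends. Simulated values are 66% to 68% for 10 to 100 women per centre.

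**4. What it could do to the result (illustration on an assumption).** Suppose that women enrolled when treatment is expected differ in LGA risk by d percentage points from those enrolled when normal care is expected, and that every enrolment follows such a guess. The arms then differ by d × (0.722 − 0.278) = 0.44d. For d of 2 to 4 points this is 0.9 to 1.8 points, or 15% to 30% of the planned six-point difference. It could act in either direction. The documents give no value for d, and it may be zero.

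**The case against.** The strongest reply is that allocation is made centrally and online after consent, so no site holds a list and no assignment is visible before randomisation. A reader might infer from the small blocks that concealment has failed. The document does not support that: it claims an unknown block size, and what is lost is unpredictability.

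Second, 39% is an upper bound. It needs strict alternation, a known position and one observer with the whole centre sequence. The wording may equally mean random order, which gives about 11%.

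Third, exploiting the sequence takes effort. Women are invited by physicians, obstetricians, midwives or diabetes nurses in hospital and community care, and any one of them may see only part of a centre's sequence. The 32-week entry limit also bounds how long a woman can be held back. The plan records age, parity, BMI, prior GDM and ethnicity for women who decline randomisation, which is a partial check, though it misses women never approached.

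Fourth, the article appeared on 17 February 2025 and does not say whether recruitment was still open, so the effect of publication itself is unknown.

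Fifth, larger blocks move the best guess only from 72% to 68%.

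All five stand as limits. None removes the tally result, which depends neither on publication nor on how the lengths are ordered. On the fifth, the larger gain is in forced allocations.

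**Conclusion.** The point holds as one of predictability. About 72% of allocations can be guessed from a tally. For someone who knows the lengths, the certain share runs from about 11% to at most 39%, depending on how the lengths are ordered and what the observer knows of the position. The stated safeguard is weak on two counts: the article prints the lengths, and secrecy does not lower the 72%.

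These figures assume that someone tracks the full sequence at a centre. A reader might go further and infer that the primary comparison is biased beyond repair. The documents show no selective enrolment, and OGTT glucose, BMI and GDM risk factors are recorded at baseline, so selection on those could be partly detected and adjusted for. This is a cheap improvement to the design, not a defect that invalidates it.

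**What to change.** - **If recruitment is still open:** for the remaining randomisations, set the system to larger blocks in random order without length 2, for example 4, 6 and 8, and keep the lengths out of documents that sites can read until recruitment closes. The cost is a system setting and a short amendment. The largest possible imbalance at a centre rises from 2 to 4 women, which matters little with 516 per arm.
- **In either case:** before analysis, prespecify a selection-bias check. For each woman, compute the probability of her arm implied by earlier allocations at her centre, and compare baseline risk (OGTT glucose, BMI, GDM risk factors including a previous LGA infant) across that probability. Add a sensitivity analysis of the primary outcome adjusted for the same variables. This needs no new data, since the Baseline characteristics section already lists them. It cannot detect selection on unrecorded features.
- **In the text:** state whether the lengths alternate strictly or are drawn at random, and do not present an unknown block size as protection while the lengths are published.
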